### Randomisation and blinding

The SEACO health round database will serve as the sampling frame, from which eligible participants are identified. Block randomisation will be carried out to assign eligible participants into one of the four arms using R software (randomizeR).^32^ Block sizes of four participants will be used in the randomisation and will be generated by a member of the research team not involved in the data collection. The interviewers will be blinded to the participant assignment to intervention arms. Participant blinding to the intervention allocation will not be possible due to the nature of the dietary intervention study. Matching of characteristics for group allocation will not be used in this study. The distribution of characteristics, such as age or gender, will be part of the feasibility assessment to gain information on the characteristics of the population willing to participate without imposing any restrictions on the intention to participate in the study. This information will be used to evaluate whether specific randomisation approaches will need to be used in future studies to ensure even distribution of key characteristics between groups.

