**Figure 1 F1:**
[figure not shown]
A flow diagram providing an overview of the study procedures.

An interim 2-month visit will take place for those in the intervention groups only, to provide reinforcement messages relating to the allocated dietary intervention and with a view to enhancing compliance with the intervention. In addition, a brief adherence questionnaire will be administered, body weight and resting blood pressure will be measured and salivary strip and spot urine samples will be collected. The same measurements and further dietary reinforcement messages will be conducted at an interim 4-month visit for the participants allocated to the intervention arms. Participants in the control arm will only have one interim visit at month 4 and will have their weight and blood pressure measured. The end of study visit (at KK, Segamat) will include the conduction of the measurements collected at baseline, including cognitive assessment, dietary assessment and collection of biological samples (blood, dried blood spots, 24-hour urine and spot urine samples, saliva samples, salivary strips). In addition, an exit group session (focus group evaluation) and a self-administered feedback questionnaire will be scheduled to evaluate the adherence to the interventions and obtain detailed feedback on the overall study protocol. Finally, the participants will be offered a token of appreciation to acknowledge their participation in the study and to compensate for travel expenses. This is usually to the value of RM 25.

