### Intervention and control arms

This dietary and behavioural intervention will focus on key components that are related to changing local dietary patterns influenced by nutritional transition trends in Malaysia. It aims to target two key components that have protective (dietary nitrate) and negative (salt intake) effects on cardiovascular and cognitive health. The intervention will target individuals with a higher Cardiovascular Disease (CVD) risk to adopt a tailored strategy to enhance daily consumption of green leafy vegetables and/or reduce salt intake. Nutritional counselling sessions with a medical doctor will be conducted at baseline to provide sustainable and effective strategies to improve dietary habits as well as monitor and address key barriers to dietary change. These sessions will be delivered in a group setting using PowerPoint slides and practical activities to educate the group on the allocated dietary intervention. All intervention groups will receive written information focused on health benefits, sources, recommended intakes and practical tips related to one of the following dietary interventions: (1) to increase dietary nitrate, (2) to reduce salt intake and (3) to increase dietary nitrate and to reduce salt intake. Those who are randomised to the salt intervention (either alone or combined) will receive a measuring spoon as an additional strategy to support individuals to understand portion size and measure salt intake, as successfully tested by an intervention study in China.^33^ Furthermore, the Ministry for Health Malaysia set out in their Salt Reduction Strategy 2015–2020 how reducing the amount of salt and sauces consumed in the home is a key priority.^34^ This provides justification for inclusion of the salt restriction spoon as an intervention strategy. The intervention groups will also receive bi-weekly text message reminders to provide reinforcement of the key dietary behaviour change messages relevant for their group allocation. Compliance will be monitored during the intermediate visits (2 and 4 months, respectively) where participants will also receive reinforcement video messages to remind participants of the key dietary advice that was discussed during the counselling sessions at baseline. Those allocated to the control group (4) will receive written information on general healthy eating and lifestyle advice based on the Malaysian dietary guidelines.^35^

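### Interviewer blinding is claimed without limit, but it cannot hold at the month-2 and month-4 visits, and at month 6 it depends on staffing the article does not state

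*Protocol article*

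**What the plan says.** The section Randomisation and blinding makes an unqualified statement: "The interviewers will be blinded to the participant assignment to intervention arms". It concedes for participants that "Participant blinding to the intervention allocation will not be possible". On the list it says "Block sizes of four participants will be used in the randomisation", to "assign eligible participants into one of the four arms", with the blocks "generated by a member of the research team not involved in the data collection".

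The visit schedule is in Study procedure: "An interim 2-month visit will take place for those in the intervention groups only, to provide reinforcement messages relating to the allocated dietary intervention". At that visit an adherence questionnaire is given, weight and blood pressure are measured, and a salivary strip and spot urine are collected. The intervention arms repeat this at month 4. For the others, "Participants in the control arm will only have one interim visit at month 4", with weight and blood pressure measured. Intervention and control arms adds that at the interim visits "participants will also receive reinforcement video messages to remind participants of the key dietary advice" from the baseline counselling, and that both salt arms are given a measuring spoon.

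Outcome measures lists month 4 as an outcome assessment for all groups and month 2 as an additional one for the intervention groups. It places both in the participant's home.

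**The concern.** A blinding statement tells readers that outcome measurement is protected from the assessor's knowledge of the arm. Here the same visits deliver the intervention and measure outcomes, and the article names no separate staff for the two jobs.

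The outcomes most open to assessor influence come at month 6. Data collectors read questionnaire items aloud and facilitate the 24-hour recall, and the cognitive tests are given then too. If a collector who made a participant's interim visits also assesses that participant at month 6, those outcomes are unblinded as well. The study is meant to supply effect sizes for a larger efficacy trial, so an unexamined blinding claim could carry forward into that design.

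The fixed block of four is a separate and lesser matter. With four arms it lets anyone who knows the earlier members of a block deduce the last one.

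**Working it through.** **Blinding by visit.** Inputs: 120 participants (Study design), 30 per group (Sample size), and visit content from Study procedure, Intervention and control arms, and Outcome measures.

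- Month 2: intervention arms only, 3 × 30 = 90 visits before drop-out. The visit itself shows that the participant is not a control. The messages concern the allocated diet, so they usually show which diet. Weight and blood pressure are taken at this visit.
- Month 4: all arms, 4 × 30 = 120 visits before drop-out. The 90 intervention participants receive reinforcement and the 30 controls do not, so the content separates control from intervention. Weight and blood pressure are taken in all arms.
- Month 6: the content is the same in all arms. Blinding depends on whether the assessor made that participant's interim visits. The article is silent.

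Visit number alone does not separate the three intervention arms. The messages, the video or the spoon do that.

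One detail needs reconciling. Table 1 marks the week-16 urine sample as spot urine but does not mark it as intervention-only, whereas Study procedure mentions only weight and blood pressure for controls at month 4. The month-4 difference in sampling therefore rests on the text. The month-2 difference and the month-4 difference in reinforcement do not depend on it.

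**Blocks of four.** First the plan's own figure: 120/4 = 30 blocks, each holding every arm once, gives 30 per arm, as stated.

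- If the exact arms of all earlier block members are known, the chance of naming the next arm is 1/4, 1/3, 1/2, then 1. The fourth is certain in all 4! = 24 orders, so 30 of 120 = 25% of allocations. The average best guess is (1/4 + 1/3 + 1/2 + 1)/4 = 0.52, against 0.25 by chance.
- If only control versus intervention is known, the fourth member's control or intervention status is certain. The exact arm is certain only when control comes last, in 3! = 6 of 24 orders (25% of blocks). The best guess at the fourth is then right with probability 6/24 × 1 + 18/24 × 1/3 = 1/2.

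**Can interim visits reveal an allocation still to be made?** The first difference in schedule comes at week 8. The mean gap between successive participants is recruitment duration/119. The article gives no duration, so I assume 13 to 52 weeks. A block then spans 3 × 13/119 = 0.3 to 3 × 52/119 = 1.3 weeks. For the mean gap between the third and fourth members to reach 8 weeks, recruitment would have to last 119 × 8 = 952 weeks, about 18 years. The fourth member is therefore allocated long before any month-2 visit to the other three.

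**Effect of a larger block.** In a block of eight with two per arm, and with size and earlier arms known, the last allocation is always certain. The seventh is certain when it matches the eighth, which has probability 1/7. That gives 1 + 1/7 = 1.14 per block, and 1.14/8 = 14.3% of allocations, against 25% for blocks of four.

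**The case against.** The strongest defence has three parts.

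First, the outcomes at months 2 and 4 leave an interviewer little room. Blood pressure is the median of three readings on a calibrated automated monitor, and weight is read from electronic scales. The recall, food frequency questionnaire and cognitive tests are done only at baseline and month 6. This stands, and it limits the harm at the interim visits.

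Second, the primary outcomes are feasibility measures reported descriptively, and the article calls its between-arm comparisons exploratory. This also stands. It lowers the stakes but does not make the blinding statement accurate.

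Third, an article condenses a fuller protocol, which may assign separate staff. That could rescue month 6, and perhaps month 4 if the person measuring is kept apart from the reinforcement and did not visit at month 2. It cannot rescue month 2, because anyone measuring at an intervention-only visit knows the participant is not a control. The point is also not an omitted detail: an affirmative statement conflicts with procedures in the same article.

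A reader might go further and infer that interim-visit knowledge lets recruiters foresee or steer allocations. The documents do not support that. The knowledge starts at week 8, after the block is filled. Prediction would need the arms of earlier participants at baseline, together with the block size and enrolment order. Arm-specific education does take place in week 1, but nothing says that recruiting staff see it in sequence. Group counselling is compatible with allocation in batches, which would limit guessing. A reader might also infer that month 6 is unblinded. The article does not say that the same staff are used, so that remains conditional.

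**Conclusion.** The claim of interviewer blinding does not hold at months 2 and 4 as the visits are described. Up to 90 and 120 participants respectively have blood pressure and weight measured at visits whose existence or content reveals at least control versus intervention. At month 6 the claim holds only if someone other than the interim visitor assesses, which the article leaves unstated.

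The block-size point is secondary. The figure of 30 of 120 (25%) certain allocations is an upper bound. It requires staff to know the block size, the order and the exact arms of the first three block members before the fourth is allocated. The documents do not show that this happens, and the interim visits come too late to cause it. Having the list generated outside data collection is good practice, but it does not prevent deduction from allocations already seen.

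The change is worth making. It corrects a stated design property and protects the interviewer-administered month-6 outcomes at little cost. It does not threaten the feasibility objectives.

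**What to change.** 1. Roster the existing data collectors so that nobody assesses at month 6 a participant they visited at month 2 or 4, and state this in the protocol. The cost is some loss of flexibility in scheduling, with no extra staff. Participants know their arm and could still disclose it, so rostering reduces the risk without removing it.
2. Restate the claim as: *assessors blinded at baseline and month 6; interim visits not blinded*. The baseline part presumes that baseline measurements are complete before the arm is disclosed, so the protocol should say when disclosure happens. The cost is a wording change.
3. Reconcile Table 1 with Study procedure on whether controls give a urine sample at month 4.
4. Use randomly varied block sizes, for example 4 and 8, not disclosed to field staff. This reduces deducibility without removing it: even a known fixed block of eight leaves 14.3% certain in the worst case. The cost is new list parameters and a slightly larger temporary imbalance between arms. If the present list is already in use, items 1 to 3 still apply.

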### Intervention and control arms

This dietary and behavioural intervention will focus on key components that are related to changing local dietary patterns influenced by nutritional transition trends in Malaysia. It aims to target two key components that have protective (dietary nitrate) and negative (salt intake) effects on cardiovascular and cognitive health. The intervention will target individuals with a higher Cardiovascular Disease (CVD) risk to adopt a tailored strategy to enhance daily consumption of green leafy vegetables and/or reduce salt intake. Nutritional counselling sessions with a medical doctor will be conducted at baseline to provide sustainable and effective strategies to improve dietary habits as well as monitor and address key barriers to dietary change. These sessions will be delivered in a group setting using PowerPoint slides and practical activities to educate the group on the allocated dietary intervention. All intervention groups will receive written information focused on health benefits, sources, recommended intakes and practical tips related to one of the following dietary interventions: (1) to increase dietary nitrate, (2) to reduce salt intake and (3) to increase dietary nitrate and to reduce salt intake. Those who are randomised to the salt intervention (either alone or combined) will receive a measuring spoon as an additional strategy to support individuals to understand portion size and measure salt intake, as successfully tested by an intervention study in China.^33^ Furthermore, the Ministry for Health Malaysia set out in their Salt Reduction Strategy 2015–2020 how reducing the amount of salt and sauces consumed in the home is a key priority.^34^ This provides justification for inclusion of the salt restriction spoon as an intervention strategy. The intervention groups will also receive bi-weekly text message reminders to provide reinforcement of the key dietary behaviour change messages relevant for their group allocation. Compliance will be monitored during the intermediate visits (2 and 4 months, respectively) where participants will also receive reinforcement video messages to remind participants of the key dietary advice that was discussed during the counselling sessions at baseline. Those allocated to the control group (4) will receive written information on general healthy eating and lifestyle advice based on the Malaysian dietary guidelines.^35^

### Outcome measures

Outcome assessments will be conducted at baseline, month 4 and month 6 for all groups, with an additional assessment visit at month 2 for those in the intervention groups. Assessments at baseline and month 6 will be conducted in clinic/at home, with remaining assessments completed in the participants own home. The same instruments will be used for measurements at each time point. Assessors are trained prior to the assessments to follow a standardised protocol. A timeline of the study procedures can be found in table 1.

**Table 1 T1:** Timeline of study procedures

Procedures	Consent/screening	Baseline Week 1	Week 2	Week 4	Week 6	Week 8	Week 10	Week 12	Week 16	Week 18	Week 20	Week 22	End of study Week 24
Inclusion/exclusion	✓												
Consent	✓												
Activities for intervention group													
Dietary education		✓											
Reinforcement at home visit		✓				✓			✓				
Group education counselling session		✓											
Home visit						✓			✓				
SMS messages			✓	✓	✓	✓	✓	✓	✓	✓	✓	✓	✓
Activities for control group													
General health promotion message		✓											
Home visit									✓				
Study measurements													
Sociodemographic		✓											
Concomitant medication check list		✓				✓							✓
Any medical events		✓				✓							✓
Physical activity (IPAQ)		✓											✓
Depression (GDS)		✓											✓
Food Frequency Questionnaire (FFQ)		✓											✓
24-hour dietary recall		✓											✓
Nitrate: urine		✓*				✓†‡			✓‡				✓*
Salt: urine		✓*				✓†‡			✓‡				✓*
Cognitive performance		✓											✓
Resting blood pressure		✓				✓†			✓				✓
Body composition		✓				✓†§			✓§				✓
Physical function		✓											✓
Blood sample and dried blood spot		✓											✓
Saliva sample and salivary strips		✓	✓†¶	✓¶	✓

*Twenty-four hour urine and spot urine samples.

†Intervention groups only.

‡Spot urine sample only.

§Body weight only.

¶Saliva strips only.

FFQ, Food Frequency Questionnaire; GDS, Geriatric Depression Scale; IPAQ, International Physical Activity Questionnaire.

#### Primary outcome

The primary outcome measures are related to feasibility and will be collected via questionnaire, review of the study procedures and by review of data collector field notes. Patient feedback, acceptance and adherence issues will be additionally assessed through qualitative focus groups conducted post intervention. The specific feasibility considerations that will be assessed in the study have been outlined in table 2. The CONSORT 2010 statement^36^ will be used to guide the reporting of the feasibility results.

**Table 2 T2:** Primary outcome: feasibility considerations to be assessed

Feasibility considerations	
Recruitment	Recruitment rates Time taken for the recruitment of participants Characteristics of recruited sample as against expected Non-response rates Reasons for non-response
Retention and completion	Retention rates Number of drops and reasons for withdrawal Follow-up response rates (2 months and 4 months follow-ups)
Feasibility of measurement tools	Time taken to fill in questionnaires Missing data from questionnaires Understanding level of procedures and measurement protocols Suitability of outcome measures Sensitivity of outcome measures to change Internal consistency of outcome measures—validation of data collection methods (24 hours vs spot urine; saliva samples vs salivary strips)
Resource capacity	Data collection and measurement equipment Field support (transportation, IT and so on) Personnel (were the right numbers of people with the right skills available when they were needed) Duration of each phase
Acceptability and adherence to intervention	Barriers to participation (collected at screening interview) Burden (reasons for not taking part/discontinuation or dropping out) Qualitative enquiry/feedback from participants and research staff Focus group evaluation—this part of the feasibility trial will separately examine the acceptability and suitability of: intervention materials; intervention timing; intervention procedures; measurement and sample collection; adherence to intervention and barriers and facilitators to dietary and lifestyle changes

#### Secondary outcomes

##### Cognitive assessment

A validated version of Montreal Cognitive Assessment test, auditory verbal learning test, categorical verbal fluency and trail making test part B will be conducted at baseline and end of study visits.

##### Blood pressure

Three consecutive measurements of resting blood pressure readings will be recorded in a sitting position using a calibrated OMRON automated monitor (OMRON HEM 907, OMRON Healthcare, Milton Keynes, UK). The median measure will be used to estimate the blood pressure. Blood pressure will be measured at all outcome assessment visits.

##### Anthropometry and body composition

Body weight will be recorded in kilograms using calibrated, electronic scales to the nearest 0.1 kg where possible. Weight will be measured at all outcome assessment visits. Height will be recorded in metres using a stadiometer and measured to the nearest 0.01 m where possible. The recordings for weight and height will be subsequently used to calculate BMI by dividing weight (kg) by height (m^2^). BMI will be calculated at baseline and end of study visits. Body composition will be measured by bioelectrical impedance. A Tanita Body Composition analyser will be used to measure body fat percentage and classification, segmental subcutaneous fat and skeletal muscle percentage (whole body, trunk, legs and arms), resting metabolism, visceral fat level and classification and body age. Body composition will be measured at baseline and end of study visits.

##### Physical assessments

The following physical assessments will be conducted at baseline and end of study visits. (1) Muscle strength will be measured by a hand grip-strength dynamometer. Using their right arm, the participant will be asked to make three measurements and an average calculated. The same process will be repeated for the left arm. (2) A 4-metre walk test will be done to assess the gait speed. Two trials will be conducted and the average measure of time in minutes will be used to assess the gait speed. (3) In the Timed Up and Go (TUG) test, the time taken for participants to rise from an armless chair (46 cm height), to walk 3 m, turn, walk back and sit down will be measured. The TUG test will be performed two times consecutively, and the average of the two scores will be used. (4) The GDS will be used to assess depressive symptoms^37^—scores range from 0 to 15, with a score of 0 to 5 indicating a normal score and a score greater than 5 suggesting depression. The IPAQ^38^ will be used to assess physical activity.

##### Dietary assessment

Conventional approaches to assessing dietary intake are associated with measurement error. There is a growing consensus that combining the use of self-report instruments (like FFQ and 24-hour recall) together with biomarker analyses could increase the accuracy of individual intake estimates, especially for episodically consumed foods.^39 40^ Thus, dietary assessment data will be collected by two methods: 24-hour recall and FFQ. Participants will complete a 1-day 24-hour recall facilitated by a trained data collector. The FFQ is a validated questionnaire used in previous dietary research in Malaysia.^41^ Information will be entered into Nutritionist Pro Software (V.7.5) and daily intake will be calculated.

